**Methodology:**

Randomized clinical trial with 52 weeks’ follow-up of patients with asthma seen in a specialized hospital for their treatment in Spain. Some 108 included patients will be divided into two groups. The intervention group will undergo more exhaustive follow-up than normal, including access to the ESTOI application, which will have various categories of attention: control of symptoms, health recommendations, current treatment and personalized action plan, PEF record, nutritional plan, and chat access with a medical team. The asthma control questionnaire ACT is the main assessment variable. Other variables to be studied include an adherence test for the use of inhalers (TAI), the number of exacerbations, maximum exhalation flow, exhaled nitric oxide test, hospital anxiety and depression scale, asthma quality-of-life questionnaire, forced spirometry parameters (FVC, FEV1, and PBD), and analytic parameters (eosinophilia and IGE). The data will be collected during outpatient visits.

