### Calculation of the sample

In order to calculate the sample size, a screening of 60 patients seen in the pneumology unit of the center was made with the ACT questionnaire, in order to learn the degree of current control of the asthma of those patients.

With a CI of 95% and a standard deviation of 4.95, the average ACT score of the patients seen in our center was 18.43 ± 1.25. The calculation of the sample size was based upon the established aims. We used the Granmo 7.12 program for two independent averages, accepting an alpha risk of 0.05 and a beta risk of 0.2 in bilateral contrast. Some 54 subjects were determined to be needed for each group in order to detect a difference equal to or greater than 3 units in the ACT questionnaire [16, 17]. We assumed a common standard deviation of 4.95 (obtained by screening in our center) and calculated a rate of loss in follow-up of 20%.

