### Variables

The main variable of the study will be ACT. Evaluation will be made of the participants in both groups, at the beginning of follow-up, at 6 months, and at 12 months. The results obtained will be compared. In addition, sociodemographic variables will be collected, such as age, sex, education level, and experience in the use of mobile applications. The study variables are detailed in Table 2.

**Table 2 Tab2:** Study variables

Variable	Description	When will it be used?
**Asthma Control Test (ACT)**	ACT is a 5-item questionnaire that assesses the level of control of asthma symptoms during the previous 4 weeks [19].	CG at each visit (v1, v2, v3) IG once a month (using the ESTOI app) and at each visit of the study (V1, V2, V3)
**Test of the Adherence to Inhalers (TAI)**	TAI is a 12-item questionnaire that assesses adherence to inhalers for patients with Asthma or COPD [20].	CG at each visit (v1, v2, v3) IG once a month (using the ESTOI app) and at each visit of the study (V1, V2, V3)
**Asthma Quality of Life Questionnaire (AQLQ)**	AQLQ is a 32-item questionnaire that assesses the quality of life of patients with asthma. Covers 4 dimensions (breathlessness, mood, social limitation and worrying) [21].	Both groups (IG and CG) at each visit (V1, V2, V3)
**The Hospital Anxiety and Depression Scale (HADS)**	HADS is a questionnaire for detecting affective disorders in hospital settings with outpatients. Is frequently used to evaluate populations with chronic diseases [22].	Both groups (IG and CG) at each visit (V1, V2, V3)
**Blood eosinophil count**	Eosinophils are actively involved in diseases caused by parasites and in allergic reactions. In the case of asthma, having eosinophils in range is usually an indicator of good control [4].	Both groups (IG and CG) at V1 and V3
**Immunoglobulin E (IgE)**	IgE is an antibody involved in airway inflammation and allergic reactions. It plays an essential role in modulating severity as a direct association between IgE concentrations and increased disease severity, bronchial hyperresponsiveness and reduced lung performance [4].	Both groups (IG and CG) at V1 and V3

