### Analysis of the data

The continuous variables are expressed as mean and standard deviation in case of normal distribution, and median and interquartile range in case of non-normal distribution. The qualitative variables are to be defined as frequencies and percentages. For comparison of the continuous variables the variance analysis method (ANOVA) or the Kruskal-Wallis test will be used. For analysis of the main assessment, the Chi-squared test will be used. Stepwise logistic regression models will be used to select the subgroup with parameters significantly associated with poor control of asthma. A priori, the factors to be included in the analysis are age, number of years suffering asthma, education level, IMC, smoking, environmental exposures, pre-BD FEV1, post-BD FEV1, FeNO, blood eosinophils, general and specific blood IgE, ACT, TAI, HAD, AQLQ, number of exacerbations, and control of comorbidities that affect asthma (GERD, rhinitis, nasal polyposis, overweight/obesity, and smoking). Statistical significance will be set at *p* < 0.05.

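### The trial is sized to compare mean ACT between arms, but the main assessment is assigned a chi-squared test, which does not address the 3-unit difference or deliver the stated 80% power

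*Protocol article*

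**What the plan says.** Two places in the protocol article name the outcome. The abstract says "The asthma control questionnaire ACT is the main assessment variable" and the Variables section says "The main variable of the study will be ACT". The Variables section schedules ACT at the start, 6 months and 12 months, and ranks none of these visits above the others.

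The section Calculation of the sample treats ACT as a continuous score: "We used the Granmo 7.12 program for two independent averages", "accepting an alpha risk of 0.05 and a beta risk of 0.2 in bilateral contrast". The target is explicit: "Some 54 subjects were determined to be needed for each group in order to detect a difference equal to or greater than 3 units" of the ACT. The spread comes from a screening of 60 patients at the centre: "We assumed a common standard deviation of 4.95 (obtained by screening in our center"). The same screening gave a mean of 18.43. A 20% loss to follow-up is allowed for.

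The section Analysis of the data has two consecutive sentences on testing. The first reads "For comparison of the continuous variables the variance analysis method (ANOVA) or the Kruskal-Wallis test will be used". The second reads "For analysis of the main assessment, the Chi-squared test will be used". The article gives no ACT category, no responder rule and no expected proportions.

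**The concern.** The sample size and the primary test concern different quantities. The sample size is for a difference between two mean scores. A chi-squared test compares frequencies across categories, so ACT would have to be cut first. The resulting p-value would refer to a difference in proportions and could not be set against the 3-unit target.

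Two things are at stake. First, cutting a continuous score discards information, so 54 per group no longer carries the 80% power claimed for it. Second, if the analysis section is followed literally, the primary result does not answer the question the trial was sized for.

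This is more than detail left to a fuller plan. The article fixes a primary test, and that test conflicts with the article's own design. An analysis plan that followed the sentence would inherit the conflict, and one that departed from it would contradict the published protocol.

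**Working it through.** **Inputs from the protocol article (Calculation of the sample):** difference 3, SD 4.95, two-sided alpha 0.05, power 0.80, loss 20%, screening mean 18.43.

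**Assumptions, because the article does not give them:** ACT is approximately normal in each arm; the control mean at the analysed visit equals the screening mean, so the means are 18.43 and 21.43; ACT is split once; the chi-squared test has no continuity correction unless stated.

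**1. Reproduce the plan's figure.**

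n per arm = 2 × (1.96 + 0.8416)² × 4.95² / 3² = 42.7, so 43 evaluable. Allowing for loss, 43 / 0.80 = 53.75, so 54. This matches the article, so the design is a comparison of means. At 43 per arm its power is 80.2% by the normal approximation and 79.3% for the t-test.

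**2. Proportions after one cut.** Suppose ACT of 20 or more counts as controlled, which puts the boundary at 19.5 on a whole-number score.

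- Control: 1 − Φ((19.5 − 18.43) / 4.95) = 0.414
- App: 1 − Φ((19.5 − 21.43) / 4.95) = 0.652
- Difference: 0.237 (unrounded); mean proportion p̄ = 0.533

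**3. Chi-squared power at 43 per arm.**

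Power = Φ{[d − 1.96 √(2p̄(1 − p̄)/n)] / √[(p₁(1 − p₁) + p₂(1 − p₂))/n]} = Φ[(0.2373 − 0.2109) / 0.1045] = Φ(0.252) = 0.60.

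Exact enumeration of the two binomials gives 59.6%, or 50.1% with a continuity correction.

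**4. Vary the boundary** (exact enumeration, uncorrected).

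| Boundary | Control v app | Power, 43 per arm | Power, 54 per arm |
|---|---|---|---|
| 15.5 | 72.3% v 88.5% | 48.9% | 57.5% |
| 17.5 | 57.5% v 78.6% | 57.4% | 66.6% |
| 18.5 | 49.4% v 72.3% | 60.9% | 69.1% |
| 19.5 | 41.4% v 65.2% | 59.6% | 68.4% |
| 21.5 | 26.8% v 49.4% | 60.7% | 69.1% |
| 22.5 | 20.5% v 41.4% | 56.8% | 66.0% |
| 24.5 | 11.0% v 26.8% | 48.1% | 56.6% |

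No boundary tried exceeds about 61% after the planned loss. With nobody lost, the best is about 69%, against 88% for the comparison of means.

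**5. Check the normality assumption.** In a simulation with scores rounded and held to 5 to 25 (scale range assumed), a cut at 20 and 43 per arm, the chi-squared test has 59.8% power. The t-test has 77.0%, because the bounds shrink the realised mean difference to 2.53.

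**6. Size needed for a binary primary at 80%.** With the proportions in step 2, n = [1.96 √(2p̄(1 − p̄)) + 0.8416 √(p₁(1 − p₁) + p₂(1 − p₂))]² / d² = 68.2, so 69 evaluable per arm (exact power 80.5%; 68 gives 79.5%). After 20% loss, 69 / 0.80 = 86.25, so 87 per arm, or 174 in all against the planned 108.

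**The case against.** The strongest reply is that the sentence just before the chi-squared one already assigns continuous variables to ANOVA or Kruskal-Wallis. ACT as sized is continuous, so a suitable comparison of mean ACT may be planned, and with two arms ANOVA is equivalent to the t-test behind the sample size. This stands in part. A reader might infer that the trial could never report a result against the 3-unit target, and that goes too far. It does not remove the conflict: the abstract uses the term main assessment variable for ACT, and the analysis section then gives the main assessment its own, different test.

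A reader might also infer that power simply falls from 80% to 60%. The documents do not support that as an unconditional statement. It needs a cut-off, a control mean, a distribution, an uncorrected test and the full planned loss, and the article fixes only the last of these.

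Two further inferences should be resisted. The Limitations section mentions exacerbations, ACT and lung function together when it discusses degree of control, but that text describes measures and does not redefine the primary outcome; the abstract and the Variables section name ACT alone. Nor is the missing cut-off a fault in itself, since a condensed article may leave a threshold to the full plan. What counts is that the stated test and the stated sample size do not match.

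**Conclusion.** The concern holds. The primary test named in the analysis section does not match the comparison of means for which the trial was sized, and both are stated in the article's own words. Whichever was intended, one of the two sections has to change.

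On size, a chi-squared test on ACT split once has at most about 60% power at 43 evaluable per arm for the shift the trial was designed to detect. The chance of missing that effect is then at least about 40%, where 20% was planned. This figure rests on the stated assumptions about means, normality and a single cut. The existence of a substantial loss does not depend on where the cut falls, because every boundary examined gives well under 80%, even with nobody lost.

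**What to change.** Replace the chi-squared sentence in Analysis of the data. Name the between-arm difference in mean ACT, with its 95% CI, as the primary analysis, using either the ANOVA already planned or a linear model adjusted for baseline ACT, at one stated visit. Twelve months is an example that fits the 52-week follow-up; the article does not choose, so the sponsor must. Move the chi-squared test on the proportion controlled to the secondary analyses.

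This costs a sentence or two. It needs no new data and no more patients, and it restores the power that 54 per group was calculated to give.

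If a binary primary is really intended, the section Calculation of the sample should say so and restate the power as about 60% or less after the planned loss. Recovering 80% would not be free: under the assumptions above it takes about 87 per arm.

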### Limitations

As this is a single-center study, the results may not be representative of the general population, which limits our ability to extrapolate the findings to different clinical settings. In an attempt to offset this limitation, and to ensure that the results are as extrapolable as possible, we will use the standards laid out in the Spanish Guide for the Management of Asthma (GEMA) [1]. To learn the degree of control of the illness we will take into account the number of exacerbations suffered in the past year, the asthma symptoms measured with ACT [19], and pulmonary function, using as measuring tools the PEF and the FEV1. With the aim of determining the degree of adherence to treatment we will use the TAI questionnaire and will review the electronic history of withdrawal from prescribed medication [1, 20]. For quality of life, we will make recourse to the AQLQ and the HAD [21, 22].

Given that the proposed intervention has simple masking, the research team and the clinical staff will be aware at all times which patients belong to which group, and this could influence the behavior of the staff as well as the manner in which the results are evaluated. As a result of randomization, it may be difficult to ensure that the groups are completely comparable in all areas.

Another limitation to bear in mind is the time stipulated for follow-up, which is limited and which may impede assessment of the effectiveness of the telemedicine program over the long-term in the control of asthma.

Finally, the participants may not comply completely with the recommendations made to them, or they may abandon the study prematurely, which would cause skewing in the results and render assessment of the real effectiveness of the telemedicine program in the control of asthma difficult. In addition, assessment of the control of asthma often involves subjective measurement of symptoms and quality of life, which could be influenced by the individual perception of the participants.

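### The secondary stepwise logistic model for poor asthma control offers parts of the control definition as predictors, without limiting them to baseline, and screens 21 distinct candidates on about 43 events

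*Protocol article*

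**What the plan says.** In the protocol article, the section on analysis of the data plans one multivariable analysis: "Stepwise logistic regression models will be used to select the subgroup with parameters significantly associated with poor control of asthma". It then fixes the candidate factors in advance. Besides demographic, exposure and comorbidity items, the list names FEV1 before and after bronchodilator, and it contains the run "general and specific blood IgE, ACT, TAI, HAD, AQLQ, number of exacerbations". Smoking appears once as a factor of its own and again among the comorbidities. Body mass index and overweight/obesity are both listed. The randomised arm is not. Significance is set at p < 0.05.

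The Limitations section says how the degree of control will be judged: "we will take into account the number of exacerbations suffered in the past year, the asthma symptoms measured with ACT [19", followed by lung function measured by PEF and FEV1.

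Table 2 schedules ACT, exacerbations and FEV1 at all three visits. The analysis section does not say which visit supplies the outcome or which supplies the predictors.

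**The concern.** Three of the four elements by which control is judged (exacerbations, ACT and FEV1) are also offered as explanations of poor control. If both sides of the model come from the same visit, those terms are likely to be selected because they help to define the outcome. They would then crowd out the factors a clinician could act on, such as adherence, comorbidities and exposures.

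The second problem is the load on the data. A long list is screened by significance in a small trial, so selected factors will often be chance findings, and their p-values and odds ratios will look better than they should.

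The third is the missing arm. If the outcome is control during follow-up, the model leaves out the one factor that the trial assigns. At stake is whether the reported risk factors for poor control can be believed.

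**Working it through.** **Patients available.** The sample-size section sets a two-sided test at 5% with 80% power. It states the target as "Some 54 subjects were determined to be needed for each group in order to detect a difference equal to or greater than 3 units". On the spread of scores it says "We assumed a common standard deviation of 4.95 (obtained by screening in our center". Attrition is put at 20%.

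- n per arm = 2 × [4.95 × (1.960 + 0.842) / 3]² = 42.7, rounded up to 43.
- Allowing for loss: 43 / 0.80 = 53.75, rounded up to 54 per arm. This reproduces the stated figure, and 2 × 54 = 108 agrees with "Some 108 included patients will be divided into two groups" in the abstract.
- Expected completers: 2 × 43 = 86.

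**Candidates.**

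- Age, asthma duration, education, body mass index, smoking, exposures, pre-bronchodilator FEV1: 7.
- Post-bronchodilator FEV1, FeNO, eosinophils, total IgE, specific IgE, ACT, TAI, HAD, AQLQ, exacerbations: 10.
- Reflux, rhinitis, polyposis, overweight/obesity, smoking: 5.
- Total 7 + 10 + 5 = 22 as listed. Counting smoking once gives 21, and merging body mass index with overweight/obesity gives 20.

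**Events (assumption).** The article gives no event count for this model. Its Background puts poor control at 50%, and I apply that rate here as an assumption.

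- 86 × 0.50 = 43 events; 108 × 0.50 = 54 if nobody is lost.
- With the share varied from 30% to 60%, the smaller outcome class is 26 to 43 of 86 patients, or 32 to 54 of 108.
- Cross-check: assume a cut between ACT 19 and 20 and normal scores with SD 4.95. The share poorly controlled is then 59% at the centre's mean of 18.43, 47% at 19.93 and 35% at 21.43 (a 3-unit gain). All lie within the range used.

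**Events per distinct candidate.** Central: 43 / 21 = 2.0. Lowest: 25.8 / 21 = 1.2. Highest: 54 / 21 = 2.6. On the listed count of 22, these become 1.95, 1.2 and 2.5.

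**Chance selection if every candidate is noise.** For independent tests at 0.05, the probability of at least one false hit is 1 − 0.95^22 = 68% (1 − 0.95^21 = 66%), with 22 × 0.05 = 1.1 expected. Two sets of simulations, with 22 independent noise predictors and selection at p < 0.05, agree:

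| Patients | Runs | Method | At least one kept | Mean kept |
|---|---|---|---|---|
| 86 | 300 | forward | 68% | 1.25 |
| 86 | 300 | backward | 65% | – |
| 108 | 300 | forward | 72% | – |
| 108 | 300 | backward | 66% | – |
| 86 | 300 | forward | 74% | 1.32 |
| 86 | 500 | backward | 69% | 1.36 |

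In the last two rows, the models that kept something showed an apparent AUC of 0.68 to 0.69, where the true value is 0.50.

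**Does removing the circular terms suffice?** Dropping ACT, exacerbations, both FEV1 terms and the second smoking entry leaves 22 − 5 = 17. Then 43 / 17 = 2.5 events per candidate, so the overload remains.

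**Overlap by timing.**

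- *Same visit:* ACT, FEV1 and the exacerbation count are on both sides of the model.
- *Predictors at the first visit, outcome at 12 months:* baseline ACT and FEV1 are earlier measurements, not parts of the later outcome. Exacerbations need care. The control judgement looks back over the past year, so at 12 months a count taken during follow-up is part of the outcome, while a count from before the first visit is not.

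**The case against.** The best defence is that the circularity is conditional. The article gives no time point. If first-visit ACT, FEV1 and earlier exacerbations are used to predict control at 12 months, this is an ordinary prognostic model, and baseline control is a natural candidate. That stands, and it is why those variables need not be removed in every case. It does not remove the point, because the stated list is not limited to baseline values.

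A reader might infer that ACT must separate the outcome perfectly and that the fit must fail. The documents do not support that. Complete separation needs poor control to be cut from ACT alone at the same visit, whereas the Limitations text describes a judgement on several elements and is not a formal definition of the logistic outcome.

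A reader might also infer that the model's output would be mostly noise. The simulations assume that no candidate has any real association. They show that false selection is frequent, not that true associations are lost, and the Background itself links adherence and comorbidities to poor control.

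On the arm, it is fair to say that the model's stated purpose is to find associated factors, not to estimate the app's effect. In a baseline description the omission hardly matters; in a follow-up model it does.

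Finally, this is a condensed article, and a fuller analysis plan may define the outcome and the visit. That is why I do not fault it for leaving those out. The candidate list and the stepwise method, however, are stated here, and a fuller plan would have to change them.

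**Conclusion.** The point holds for a secondary analysis. As listed, the candidates include elements of the outcome, one factor appears twice, two others overlap, and the arm is missing. The circularity applies to same-visit data, which the text does not exclude. The overload applies under either timing: about 43 events for 21 distinct candidates, roughly 1 to 2.5 events each, and a 65 to 74% chance of keeping at least one false factor if all were noise. These figures rest on an assumed 50% rate of poor control in 86 completers (26 to 54 in the smaller outcome class over the range examined) and on independent candidates.

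It should be corrected but is not critical. A reader might infer that the trial's main result is compromised. It is not: the between-arm comparison of ACT does not depend on this model, and the sample size reproduces.

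**What to change.** State the visit and the outcome for the model, then follow one of two routes.

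- **Follow-up outcome** (for example, control at 12 months): use first-visit predictors only and include the randomised arm. Baseline ACT, baseline FEV1 and exacerbations before the first visit may stay.
- **Cross-sectional outcome:** remove every component of the control definition from the candidates.

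In either case, list smoking once and keep only one of body mass index and overweight/obesity. Replace stepwise selection with about 4 to 5 pre-specified factors, or with a penalised logistic model over the remaining list, and label the result exploratory. Five factors on 43 events give 43 / 5 = 8.6 events each, or 43 / 6 = 7.2 with the arm added.

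The cost is a rewording of a few sentences, with no new data, patients or visits. The downside is that the short pre-specified set examines fewer factors.
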